### Sample size

The IY-T service delivery team have the capacity to deliver two groups for this feasibility TwiCS. Each IY-T group aims to recruit 12 parent-child dyads (hereafter referred to as enrolees) and retain 10 participants. We have therefore based our sample size to be randomised (*n* = 240) on achieving these numbers (24 enrolees total, or 12 enrolees per group) (see below for details on how these numbers have been derived).

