### Implementation

Figure 1 presents how study participants will be drawn and randomised from the BiBBS cohort. A Standard Operating Procedure (SOP) for recruitment of participants was developed for this study. Participants randomised to intervention will initially be contacted by a designated researcher from the BiBBS team, who will confirm their eligibility and ask if they consent to their details being passed onto the IY-T team at Barnardo’s. Those who cannot be contacted after four attempted contacts will be recorded as ‘unable to contact’ (Box A). For each individual woman who is contacted, verbal consent will be sought for their details to be shared with the Incredible Years team. Those who are contacted, but who decline consent will not be followed up and will be recorded as having been offered the intervention but declined (Box B).

For those who agree to the referral, the BiBBS team will pass on the referral to the IY-T team who will then re-contact them by telephone. If participants are not able to be contacted at this stage, they are recorded as such (Box C). If IY-T assesses the referral as ineligible, they are recorded as such (Box D); this should be unlikely, however, circumstances may change, e.g. a child becomes ‘too old’ or a child is removed from the parents. We will therefore record any occurrences of this, with reasons where possible. If they can be contacted, this phone call will allow the IY-T team to provide them with more detail about the specific programme available to them and check the eligibility of these participants. If the participant accepts the offer, a home visit with one of the IY facilitators will be arranged. More information about the programme will also be sent out to all women who accept the offer of a home visit. If parents initially accept the offer from BiBBS, but not from IY-T, they will be recorded as having been offered the intervention but declined (Box E).

The numbers randomised (*n* = 240) and offered IY-T (*n* = 120) in this feasibility study aim to fill two IY-T courses (*n* = 24). If the number of study participants is not sufficient to support optimal group sizes (12 per group), the IY-T team may ‘top up’ groups by including parents referred to them from other services. These parents are not study participants and will not be included in the research.

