### Feasibility outcomes

We have based the feasibility outcome targets on data from two key sources. The first relates to a postnatal data collection sweep conducted as part of the main BiBBS cohort study. The second is information on rates of IY-T enrolment, participation and completion (where an ‘enrolee’ is referred and seen face to face in at least one pre-course contact, a ‘participant’ is someone who attends at least 1 week of the groups, and a ‘completer’ is someone who attends at least 8 of the 13 group-based sessions) reported by Barnardo’s and the Better Start Bradford Innovation Hub (see https://borninbradford.nhs.uk/what-we-do/improving-health/bsb-innovation-hub/) Table 1.

**Table 1 Tab1:** Target figures

Projected target figures	Rationale for target figures
120 randomised to intervention → 84 women are contactable]	80% of women were contactable for the BiBBS postnatal sweep, which takes place approximately 12 weeks after recruitment into BiBBS. We will contact women 1–3 years after recruitment into BiBBS, and so we have set our rate to be lower at 70%.
84 women contacted → 44 women consent to the referral → 22 women enrol	On average, the rate of conversion from referral to enrolee in IY-T is 52%. We therefore anticipate that 52% of randomised BiBBs participants will agree to be referred, and 50% of those referred will enrol into the programme.
22 enrolees → 20 enrolees go on to participate	On average, 89% of enrolees to IY-T are converted into participants. We have set a target of 90% of randomised enrolees to be converted into participants.
20 participants → 12 participants go on to complete	60% of participants go on to complete IY-T. We have set our rate to be 60%.

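### The 240 to be randomised is justified as achieving 24 enrolees, but the protocol's own derivation gives 22

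*Protocol article*

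**What the plan says.** Three places in the protocol article bear on this.

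- **Sample size.** The delivery team can run two groups. "Each IY-T group aims to recruit 12 parent-child dyads (hereafter referred to as enrolees) and retain 10 participants". The 240 to be randomised is said to rest "on achieving these numbers (24 enrolees total, or 12 enrolees per group"), with the derivation given further on.
- **Implementation.** The same figure appears again: "The numbers randomised (*n* = 240) and offered IY-T (*n* = 120) in this feasibility study aim to fill two IY-T courses (*n* = 24"). The paragraph goes on to allow groups that fall short of 12 to be topped up with parents referred from other services. It states that those parents are not study participants and are left out of the research.
- **Feasibility outcomes, Table 1.** This is the derivation. Of 120 allocated, 84 are contactable; then "84 women contacted → 44 women consent to the referral → 22 women enrol"; then "22 enrolees → 20 enrolees go on to participate"; and 12 of those 20 complete.

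The Feasibility outcomes section defines the terms. An enrolee has been referred and seen face to face at least once before the course. A participant attends at least one week. A completer attends at least 8 of the 13 sessions.

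**The concern.** One defined quantity, the number of enrolees expected from 120 women allocated to the intervention, has two values. The value used to justify the sample size (24) is not the value that the derivation produces (22).

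This is the only justification given for the number randomised, and a main use of a feasibility study is to inform the size of the next one. A reader who takes the Sample size section at face value would infer an enrolment yield of 24/120 = 20% of women allocated. The protocol's own inputs imply 18.2%. The two statements should agree before anyone plans a larger trial from them.

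**Working it through.** **Inputs**

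- Allocated to intervention: 120 of 240, 1:1 (Implementation; Randomisation).
- Stated basis: 24 enrolees, 12 in each of two groups (Sample size; Implementation).
- Contactable: 70%. The article lowers this from the 80% seen in the postnatal sweep because contact comes later: "We will contact women 1–3 years after recruitment into BiBBS, and so we have set our rate to be lower at 70" per cent (Table 1).
- Referral and enrolment: "We therefore anticipate that 52% of randomised BiBBs participants will agree to be referred, and 50% of those referred will enrol into the programme" (Table 1). The text says 52% of those randomised, but the table applies the 52% to the 84 contacted.
- Enrolee to participant 90%; participant to completer 60% (Table 1).

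**Reproducing Table 1**

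- Contactable: 120 × 0.70 = 84
- Agree to referral: 84 × 0.52 = 43.7, printed as 44
- Enrol: 44 × 0.50 = 22 (unrounded, 120 × 0.70 × 0.52 × 0.50 = 21.84)
- Participate: 22 × 0.90 = 19.8, printed as 20
- Complete: 20 × 0.60 = 12

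Table 1 is internally correct, and it gives 22 enrolees. Starting from 24 enrolees, the next step would be 24 × 0.90 = 21.6 participants rather than 20, so the rest of the table also follows from 22.

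**Number needed for an expected 24**

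- Yield per woman allocated: 0.70 × 0.52 × 0.50 = 0.182
- 24 / 0.182 = 131.9, so 132 allocated to intervention and 264 randomised. The protocol has 120 and 240, so the requirement is 10% larger.

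**Other readings of the rates**

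| Reading | Expected enrolees from 120 | Consistent with Table 1? |
|---|---|---|
| 70%, 52%, 50% | 21.8 | Yes |
| 70%, 52%, 52% | 22.7 | No, second step is 50% |
| 70%, 50%, 50% | 21.0 | No, first step is 52% |
| 80%, 52%, 50% | 25.0 | No, contact rate was set at 70% |
| 52% of all randomised, then 50% | 31.2 | No, contradicts 84 → 44 |

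Only the last two readings reach 24, and both contradict figures in the table.

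**Spread around the expectation (not claimed by the protocol)**

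If women respond independently and the Table 1 rates are the true values, enrolees follow Binomial(120, 0.182). The chance of at least 24 is then 0.34, and the central 95% range is about 14 to 30. Using 22/120 as the yield gives 0.35. Holding the 84 contacted fixed gives 0.33, as does holding the 44 referred fixed.

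**The case against.** Most of the case on the other side stands, and it limits how far the point goes.

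- **The count of 24 is not a success criterion.** A reader might infer that a study performing exactly as projected would be judged a recruitment failure. The text does not support that. Feasibility outcomes sets the green and amber levels as percentages (contamination has its own under-5% rule), and a run of 120, 84, 44, 22, 20 and 12 meets the projected rates. Table 2 is not readable here, but the text says that it summarises the same targets.
- **Top-up protects group size.** Implementation foresees study numbers too small to fill the groups and provides for it, so delivery is not at risk. This does not reconcile the two figures, because top-up parents are expressly not study participants and cannot be among the enrolees that 240 randomised women are said to yield.
- **The aim of retaining 10 participants per group is not an error.** A reader might take it to mean 10 retained to completion and set it against Table 1's 12 completers in total. Under the article's own definition a participant attends at least one week, so 10 per group is 20, which is Table 1's figure.
- **The one-in-three chance should not carry the argument.** The protocol makes no probability claim. The figure needs independence and exactly known rates, and any design sized on an expectation has only roughly an even chance of reaching it. The mismatch between 22 and 24 needs none of these assumptions.

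**Conclusion.** Wrong as written, and minor. The protocol says that 240 randomised (120 offered) is based on achieving 24 enrolees, while the derivation it relies on yields 21.8, printed as 22, or 11 per group. No reading consistent with Table 1's own counts and its 70% contact rate gives 24. The shortfall is two enrolees. Expressed as sample size, it is 132 against 120 in the intervention arm.

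This conclusion rests only on printed figures and multiplication. The 34% chance of reaching 24 and the 14 to 30 range rest on the further assumptions given with them. No outcome, threshold, allocation rule or analysis is affected. The participant figure of 20 agrees between Sample size and Table 1, and nothing here suggests that the study would fail its own criteria.

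**What to change.** In Implementation and in Sample size, replace the claim that the randomised number achieves 24 enrolees with one that matches Table 1. For example: 120 women allocated to the intervention are expected to yield about 22 study enrolees (11 per group), 20 participants and 12 completers; the two courses offer 24 places, and about 2 of these are expected to be filled through the existing top-up provision by parents who are not in the study.

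Optionally, add that the chance of at least 24 study enrolees is about 34%, with a 95% range of about 14 to 30, assuming that women respond independently and the Table 1 rates are true.

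If 24 study enrolees is really the intended basis, the alternative is to raise the number randomised to about 264. The restatement is the cheaper course: it changes wording only, and its one cost is a slightly less favourable headline figure.

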### Feasibility outcomes

We have based the feasibility outcome targets on data from two key sources. The first relates to a postnatal data collection sweep conducted as part of the main BiBBS cohort study. The second is information on rates of IY-T enrolment, participation and completion (where an ‘enrolee’ is referred and seen face to face in at least one pre-course contact, a ‘participant’ is someone who attends at least 1 week of the groups, and a ‘completer’ is someone who attends at least 8 of the 13 group-based sessions) reported by Barnardo’s and the Better Start Bradford Innovation Hub (see https://borninbradford.nhs.uk/what-we-do/improving-health/bsb-innovation-hub/) Table 1.

**Table 1 Tab1:** Target figures

Projected target figures	Rationale for target figures
120 randomised to intervention → 84 women are contactable]	80% of women were contactable for the BiBBS postnatal sweep, which takes place approximately 12 weeks after recruitment into BiBBS. We will contact women 1–3 years after recruitment into BiBBS, and so we have set our rate to be lower at 70%.
84 women contacted → 44 women consent to the referral → 22 women enrol	On average, the rate of conversion from referral to enrolee in IY-T is 52%. We therefore anticipate that 52% of randomised BiBBs participants will agree to be referred, and 50% of those referred will enrol into the programme.
22 enrolees → 20 enrolees go on to participate	On average, 89% of enrolees to IY-T are converted into participants. We have set a target of 90% of randomised enrolees to be converted into participants.
20 participants → 12 participants go on to complete	60% of participants go on to complete IY-T. We have set our rate to be 60%.

**Table 2 Tab2:**
[figure not shown]

[figure not shown]
Feasibility objectives and outcomes

Table 1 summarises our target figures and how these were decided upon, and Table 2 summarises these targets and outlines how feasibility objectives will be assessed. In addition to the above, we also aim to assess contamination (any overlap between allocated control group, and non-randomised intervention group participants) and aim for this to occur in <5% of the sample. This is based on an estimate that <5% contamination has a negligible effect on the required sample size for a trial [33]. A RAG rating system has been applied to support the feasibility assessment of each objective: to be rated as green (achieved), amber (partly achieved) and red (not achieved). For an objective to be achieved and rated green, it must reach the percentage level specified above (e.g. 70% for contactable women, 50% for converting randomised participants into referrals). The levels at which we reach amber are equal to the green target, minus 20%. This is except for the rate for contamination (objective 1.2), where the rates are set on achieving less than 5% contamination.

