### Objectives

This study aims to establish whether it is feasible to conduct a TwiCs evaluation of a parenting programme for parents of toddlers initially recruited during pregnancy into the BiBBS birth cohort.

The specific objectives address key uncertainties. A Red, Amber, Green (RAG) rating system has been applied to support the feasibility assessment of each objective: to be rated red (not achieved), amber (partly achieved), and green (achieved). The objectives are:To establish whether TwiCS methodology can be implemented to create a control and intervention arms, whilst documenting any incidences of contamination (i.e. control participants that are offered or receive the intervention).To establish whether satisfactory rates of intervention uptake are achieved among participants allocated to the intervention.To establish whether satisfactory rates of retention of participants in the intervention can be achieved.

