### Randomisation

Eligible participants in the BiBBS cohort will be individually randomised 1:1 to the intervention (*n* = 120) or control group (*n* = 120), using blocked randomisation with stratification by child age (1 year or 2 years at the time of randomisation) and ethnicity (White British, South Asian, or other). The six allocation sequences (one for each stratum) will be generated using Stata/SE v17.0 (for Windows 64-bit x86-64) or later, using the user-written Stata command ralloc (Ryan, 1997).

We will draw a stratified random sample of 240 participants from all eligible participants in the BiBBS database, with sampling fractions (approximately) proportional to the distribution of the six randomisation strata in the eligible cohort population. The *n*_*i*_ sampled participants in stratum *i* will then be randomly sorted and matched against the first *n*_*i*_ allocations in the allocation sequence for stratum *i*.

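### The sample-size reason given for the 5% contamination limit does not hold at the plan's own projected participation of 17%

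*Protocol article*

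**What the plan says.** In the protocol article, Feasibility outcomes (text after Table 2), contamination is an overlap between the control arm and women taking part in programme groups outside the randomised allocation. The authors "aim for this to occur in <5% of the sample" and explain: "This is based on an estimate that <5% contamination has a negligible effect on the required sample size for a trial". An outside source is cited, and nothing in the text relates the limit to uptake in the intervention arm. The Objectives section defines contamination more widely, as "control participants that are offered or receive the intervention".

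Table 1 in the same section projects the flow through the intervention arm: "120 randomised to intervention → 84 women are contactable", then "84 women contacted → 44 women consent to the referral → 22 women enrol", then "22 enrolees → 20 enrolees go on to participate", then "20 participants → 12 participants go on to complete". A participant is a woman who attends at least one week of the groups.

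Contamination has its own red, amber or green rating (objective 1.2). Uptake and retention are rated under separate objectives.

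**The concern.** Five per cent contamination is a small loss when nearly everyone allocated to the intervention receives it. Here about one woman in six is expected to attend at all. Women allocated to the offer differ from controls only through the difference in attendance, so 5 percentage points of control attendance must be set against 16.7 points, not against 100. That is 5/16.7, or about 30% of the contrast.

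The limit is justified by its effect on the size of a later trial, and the Discussion presents that later, larger trial as the next step if this one is feasible. The Background adds that the delivery team keeps taking its usual community referrals during the study, so contamination is a real possibility. A green rating that rests on this reason could lead planners of the later trial to leave contamination out of their sample-size calculation.

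**Working it through.** **Inputs**
- Arm sizes: 120 and 120 (Randomisation).
- Rates in Table 1: 70% contactable, 52% agree to referral, 50% of those enrol, 90% of enrolees participate, 60% of participants complete.
- Contamination limit: below 5% (Feasibility outcomes).

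**Step 1. Reproduce the plan's own figures.** 120 × 0.70 = 84.0; × 0.52 = 43.7; × 0.50 = 21.8; × 0.90 = 19.7; × 0.60 = 11.8. Table 1 gives 84, 44, 22, 20 and 12, so the cascade reproduces. Projected attendance of at least one session is p1 = 20/120 = 16.7%.

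**Step 2. Formula.** Let p0 be attendance among controls. If benefit comes only through attendance and is the same for attenders in either arm, the as-allocated difference is proportional to p1 − p0 and the required sample size to 1/(p1 − p0)². The inflation due to contamination alone, relative to p0 = 0, is [p1/(p1 − p0)]². It does not depend on effect size, alpha or power.

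**Step 3. Benchmark at full uptake.** With p1 = 100% and p0 = 5%: (1/0.95)² = 1.11.

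**Step 4. At the projected uptake, p1 = 16.7%.**

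| Control attendance p0 | Calculation | Multiplier |
|---|---|---|
| 1% | (16.67/15.67)² | 1.13 |
| 2% | (16.67/14.67)² | 1.29 |
| 5 of 120 (4.2%, largest count below 5%) | (20/15)² | 1.78 |
| 5% (the limit itself) | (16.67/11.67)² | 2.04 |

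**Step 5. Other definitions of uptake**, at 5 of 120 and at 5%: enrolees (22/120) give 1.67 and 1.89; completers (12/120) give 2.94 and 4.00.

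**Step 6. If controls who were only offered the programme also count.** Assume that offered controls attend at the service rates quoted in Table 1, 0.52 × 0.89 = 0.46. Then 5% offered means about 2.3% attending and a multiplier of (16.67/14.35)² = 1.35. At 5 of 120 offered, about 1.9% attend and the multiplier is (16.67/14.74)² = 1.28.

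**Step 7. Illustration in absolute numbers.** The protocol gives no effect size, alpha or power for a later trial. Assume a 0.5 SD benefit in attenders, two-sided alpha of 0.05 and 80% power. The as-allocated difference without contamination is 0.5 × 0.1667 = 0.083 SD, which needs 2,261 women per arm. With 5 of 120 controls attending it is 4,019, and at 5% it is 4,614. The ratios, 1.78 and 2.04, match step 4.

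**The case against.** - **This is a feasibility study.** It makes no effectiveness comparison and sizes no later trial. The ratings only support the assessment, and counts, percentages and Wilson intervals are planned for the feasibility outcomes. Planners of a later trial will hold attendance data for both arms and can work out the inflation themselves. This stands, and it keeps the point at moderate severity.
- **Low uptake matters far more.** Under the same formula, 16.7% uptake with no contamination already multiplies the sample size by (120/20)² = 36 relative to full uptake. That is true, and the protocol tests uptake separately. The contamination factor comes on top of it, and it is the one that the protocol calls negligible.
- **The top figure needs every contaminated control to attend and gain fully.** This also stands. Under the wider definition in the Objectives, or with weaker attendance among controls, the factor falls (step 6), and at 1–2% contamination it is modest.
- **The cited source and Table 2 are not at hand.** The source may attach conditions to its estimate. The point is therefore limited to the unqualified use of that estimate next to this uptake, which the text itself shows.

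An analysis that estimates the effect in attenders would not remove the problem, because it has the same p1 − p0 in its denominator.

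**Conclusion.** The stated reason for the limit does not hold on the plan's own figures. Within the permitted range the multiplier runs from near 1 to 1.78 at the largest passing count, and approaches 2.04 at the limit, against 1.11 at full uptake. This assumes an as-allocated comparison, no benefit without attendance, equal benefit for attenders in both arms, and the control arm as the denominator.

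A reader might infer three stronger things that the documents do not support:
- **That the limit will double a later trial.** Near-doubling is the top of the permitted range under the narrower, attendance-like definition. The Objectives also count women who were only offered the programme.
- **That a green rating clears contamination as a threat to a full trial.** The protocol does not say that this rating alone licenses one.
- **That 5% refers to all 240 women.** That would let 11 controls attend and give (20/9)² = 4.94. The wording does not settle the denominator, and contamination can occur only among controls, so this figure is not relied on.

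Severity: moderate.

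**What to change.** 1. Remove the negligible-effect justification, or qualify it by stating that it does not hold at the projected uptake.
2. For this purpose, count contamination as attendance of at least one session. Report controls who were only offered the programme separately.
3. Beside the rating, report attendance in each arm over all randomised women, the difference with a 95% confidence interval, and the multiplier [p1/(p1 − p0)]². Interpret objective 1.2 jointly with uptake.
4. Counts below 5 are to be suppressed (Statistical methods). In that case give the multiplier as an upper bound. At the projected uptake, at most 4 control attenders means at most (20/16)² = 1.56.

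A green rule that requires control attendance under 5% of intervention-arm attendance is tempting but should not be adopted. With 20 attenders, one control is exactly 5%, so only zero would pass. A single cross-over would decide the rating, although the Wilson 95% interval for 1/120 runs from about 0.15% to 4.6%, and the deciding counts would be suppressed. If the limit is reset, the sponsor should choose a tolerable multiplier and derive the limit from it.

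Cost: wording and one line of analysis, using programme records that the protocol already plans to link to cohort participants (Data collection and management). The downside is that a green on contamination becomes less reassuring.

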A feasibility study is necessary at this stage due to four key uncertainties about the TwiCS design in this setting. First, IY-T delivery agents usually receive their referrals from their work with the local community. Implementing a TwiCS will introduce a procedural change for both the BiBBS team, and for IY-T’s normal referral processes. Second, due to the timing of recruitment to BiBBS and the timing of recruitment to the intervention (where participants are eligible when they have a child aged 12–36 months old), participants will be contacted between 12 and 36 months *after* they have enrolled in the BiBBS cohort. This delay introduces an uncertainty about the rate of intervention take up. Regular NHS tracing means that participants’ home addresses and children’s health status will be up to date, but phone numbers may have changed. Third, contamination (where participants who are allocated to the control group receive the intervention) may occur in this study since IY-T will still receive their usual referrals from the community during the implementation of the TwiCS; however, the level at which this may occur remains unknown. Finally, previous RCTs of parenting programmes have suffered poor take up and attendance of the intervention, particularly for parents in disadvantaged areas, and parents with a higher level of need (e.g. due to low mood) [23, 24]. We therefore need to test the rates of participation and completion of the intervention to inform the feasibility of a larger evaluation, particularly in a disadvantaged setting.

In line with previous feasibility TwiCS studies, we will test the feasibility of recruiting to the trial, the acceptability of trial processes, and the acceptance rate of the intervention and resulting sample sizes. It is not necessary for us to test the feasibility of recruiting to a cohort, nor the fidelity of intervention delivery [25–27], since the BiBBS cohort study already successfully recruits a large, representative, and diverse sample of mothers [17], and IY-T has been delivered with high fidelity in the study site since September 2018.

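### The uptake and retention RAG levels can all be green with about 16–17% of allocated women attending and about 10% completing, and no visible level is set on the allocated denominator

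*Protocol article*

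**What the plan says.** The Objectives section asks whether "satisfactory rates of intervention uptake are achieved among participants allocated to the intervention". The Current study rationale adds that the study will test "the acceptance rate of the intervention and resulting sample sizes", and that rates of participation and completion are needed to judge a larger evaluation.

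Table 1 (Feasibility outcomes) gives the targets as a chain. It starts with "120 randomised to intervention → 84 women are contactable", continues with "84 women contacted → 44 women consent to the referral → 22 women enrol", then runs from 22 enrolees to 20 participants and from 20 participants to 12 completers. A participant attends at least one week; a completer attends at least 8 of 13 sessions.

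The text under Table 2 sets the rating: "For an objective to be achieved and rated green, it must reach the percentage level specified above". Its examples are 70% for contactability and 50% for turning randomised women into referrals. Amber is the green level minus 20%. Contamination has its own limit, under 5% of the sample, justified by a negligible effect on the sample size that a trial would need.

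The referral denominator is stated in two ways. The Table 1 counts use contacted women (44 of 84). The Table 1 rationale says "We therefore anticipate that 52% of randomised BiBBs participants will agree to be referred, and 50% of those referred will enrol into the programme", and the 50% example under Table 2 also refers to randomised women.

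**The concern.** A conditional chain can look healthy at each link and still deliver little at the end. Levels of 90% (enrolee to participant) and 60% (participant to completer) sound high, but they apply to 22 and 20 women out of 120.

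In a trial within a cohort, women who cannot be reached or who decline stay in their allocated arm. The treatment contrast in a later trial is therefore governed by attendance among all allocated women, and that is also the population named in objective 2. The visible text sets no level on that proportion.

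The protocol already uses required sample size as its yardstick for contamination. It does not apply the same yardstick to uptake, which at these targets dilutes the effect far more.

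**Working it through.** **Inputs.** Allocation: "individually randomised 1:1 to the intervention (*n* = 120) or control group (*n* = 120"), from Randomisation. Step rates from Table 1: 70% contactable, 52% agree to referral, 50% enrol, 90% attend, 60% complete. Referral green level of 50% and contamination limit of 5%: text under Table 2.

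**1. Reproduce Table 1.**
- 120 × 0.70 = 84.0
- × 0.52 = 43.7, shown as 44
- × 0.50 = 21.8, shown as 22
- × 0.90 = 19.7, shown as 20
- × 0.60 = 11.8, shown as 12

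All five counts reproduce.

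**2. Put the end points on the allocated denominator (Wilson 95% intervals).**
- Attend at least once: 20/120 = 16.7% (11.1% to 24.4%)
- Complete: 12/120 = 10.0% (5.8% to 16.7%)

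**3. Vary the referral reading.**

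| Referral level | Attend | Complete |
|---|---|---|
| 52% of contacted (Table 1 counts) | 20/120 = 16.7% | 12/120 = 10.0% |
| 50% of contacted | 18.9/120 = 15.8% | 11.3/120 = 9.5% |
| 50% of randomised | 27/120 = 22.5% | 16.2/120 = 13.5% |

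The last row is 120 × 0.50 = 60 referred, × 0.50 = 30 enrolled, × 0.90 = 27, × 0.60 = 16.2. The readings also conflict: Table 1's own 44 referrals are 44/120 = 37% of randomised women, which would miss a 50% green level on that denominator.

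**4. All-amber minimum (52% of contacted as the green referral level).** The text does not say whether minus 20% means points or a relative reduction.
- Points: 0.50 × 0.32 × 0.30 × 0.70 = 3.4% attend; × 0.40 = 1.3% complete.
- Relative: 0.56 × 0.416 × 0.40 × 0.72 = 6.7% attend; × 0.48 = 3.2% complete.

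**5. Consequence for a comparison as allocated.** Assumptions, not in the documents: benefit only in attenders, and arms compared as allocated. With attendance p1 in the intervention arm and p0 in the control arm, the effect shrinks by (p1 − p0), so the sample grows by 1/(p1 − p0)².
- p1 = 0.167, p0 = 0: 1/0.1667² = 36. At the Wilson limits: 1/0.2435² = 17 and 1/0.1106² = 82.
- p1 = 0.225, p0 = 0: 1/0.225² = 19.8.
- p1 = 1, p0 = 0.05: 1/0.95² = 1.11. This is the setting in which 5% contamination is close to negligible.
- p1 = 0.167, p0 = 0.05: 1/0.1167² = 73, which is (0.1667/0.1167)² = 2.04 times the 36 above.

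The contamination lines take 5% as the share of control women who attend.

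**6. Illustrative totals** (further assumptions: two-sided 5%, 80% power, 1:1, standardised effect in attenders).

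| Effect | Full uptake | 16.7% uptake |
|---|---|---|
| 0.2 SD | 786 | 28,256 |
| 0.3 SD | 350 | 12,560 |
| 0.5 SD | 126 | 4,522 |
| 0.8 SD | 50 | 1,766 |

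Apart from rounding, the ratio is the same in every row; only the absolute totals depend on the assumed effect.

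**The case against.** Several points on the other side stand.

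- Table 2, which sets out how each objective is assessed, is not shown. A level on the allocated denominator there cannot be ruled out, although the text says that Table 2 summarises the Table 1 targets.
- A reader might infer that every RAG step is rated on survivors. That is not so: contactability is rated on all 120, contamination is a separate criterion, and the referral level is worded on randomised women.
- A reader might also take 17% and 10% as what all-green means. Green means reaching or exceeding each level. These are the values at the targets, and the minimum depends on the referral reading.
- No visible rule combines the ratings or declares a full trial feasible. The RAG system is there to support the assessment of each objective.
- The end-point proportions are not hidden. Statistical methods commits to raw numbers, percentages, Wilson intervals and a flow diagram, so any reader can divide by 120.
- Capacity limits what this study can show. Two groups of 12 are 24/120 = 20% of allocated women, and even if all 24 attended the factor would be 1/0.20² = 25. A green level tied to tolerable dilution could be out of reach here.

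These points limit the claim but do not remove it. Figures that can be derived are not figures that are judged, and the visible levels do not judge uptake in the population that objective 2 names.

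**Conclusion.** The point holds in limited form. On the visible text, all uptake and retention steps can be green with about 16–17% of allocated women attending and about 10% completing, or 22.5% and 13.5% if referral is read as 50% of randomised women. If only attenders benefit and arms are compared as allocated, the sample needed is about 36 times that of full uptake (about 20 times at 22.5%). At 16.7% uptake, 5% contamination roughly doubles it again, so the stated basis for the contamination limit does not carry over to the target uptake.

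A reader might conclude that the study could declare feasible a trial that is not. The documents do not support that: they give no effect size, power, eligible cohort size or maximum sample, and no rule turning the ratings into a decision. The inconsistent referral denominator is a definite defect and rests on no assumption.

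**What to change.** 1. Add two pre-specified rated outcomes: attendance (at least one session, out of the 120 allocated) for objective 2, and completion (at least 8 sessions, out of the 120 allocated) for objective 3. Keep the stepwise rates as diagnostics of where women are lost. Set the levels before results are seen.
2. Report the implied inflation 1/(p1 − p0)² with an interval, using attendance in both arms and stating the assumption about benefit in non-attenders. Reconsider the justification of the 5% contamination limit in the same terms.
3. State one denominator for the referral criterion and make Table 1, its rationale and the text under Table 2 agree. State also whether minus 20% means points or a relative reduction.

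Cost: protocol wording and two extra proportions. Enrolment, participation and completion data are already to be linked to cohort participants, and contamination is already to be documented. Setting the new levels needs a view on how much dilution a full trial could tolerate, which requires an assumed effect that the documents do not give. A condition that the resulting sample must fit the eligible cohort cannot be set from the documents either. The downside is that feasibility becomes harder to claim.
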